## Abstract

**Background:** The ageing of the population and the progressive increase in chronic diseases represent a major challenge for healthcare systems. The community nurse case manager (CNCM) is emerging as a key figure to provide comprehensive and continued care for complex and pluripathological chronic patients (CPCPs), especially after hospital discharge. **Objective:** The aim of this study is to pilot CNCMs in assisting CPCPs and assess their effects on functional capacity, cognitive performance, quality of life, readmissions, clinical parameters, satisfaction with home care, and caregiver overload. **Methods:** A comparative study will be carried out at two health centres in Salamanca (Spain). In both centres, CPCPs will continue to receive the interventions included in the Castilla y León Health System Portfolio from their primary care (PC) nurses. In the intervention centre, case management provided by a CNCM will be added. We will recruit 212 CPCPs with cardiac or respiratory disease and/or diabetes mellitus who are dependent for basic activities of daily living and have a programmed hospital discharge. An initial assessment will be performed at home after discharge, followed by assessments at 3, 6, and 12 months. **Expected results:** The intervention is anticipated to improve all study outcomes. **Discussion:** CNCMs may contribute to more proactive and individualised follow-up care for CPCPs and their caregivers, improving care coordination. **Conclusions:** This study will help to evaluate the feasibility and clinical relevance of incorporating the CNCM’s role into PC. This study was registered at ClinicalTrials.gov with the identifier NCT06155591. The date of trial registration was 24 November 2023.

## 1. Introduction

Population ageing is a growing challenge [1,2]. Spain is the fourth European country with the highest proportion of people aged 65 and over, currently accounting for 17% of the total population, with projections reaching 37% in 2049 [3,4]. This trend will lead to an increased prevalence of chronic diseases and, consequently, a higher healthcare demand and resource consumption [5].

Chronic diseases, characterised by their prolonged course (lasting more than six months), slow progression, and multifactorial origin, significantly affect patients’ quality of life [6,7]. Among the most prevalent conditions are cardiovascular and respiratory diseases, as well as diabetes mellitus (DM), which account for 80% of healthcare demand and 90% of mortality in Europe [8]. Furthermore, they represent the leading cause of disability and healthcare expenditure, posing a challenge for both individuals and healthcare systems [9,10].

Complex and pluripathological chronic patients (CPCPs) often present with multiple comorbidities, frailty, and clinical vulnerability, alongside a progressive decline in functional capacity [11,12,13]. This has a significant impact on healthcare demand, with considerable social and economic repercussions [9,14]. The CRONICOM project [15] revealed that 61% of patients hospitalised in internal medicine units were classified as complex chronic patients, and 40% were pluripathological, showing a deterioration in quality of life and an increased dependency following each hospital admission [16,17]. In this regard, various studies highlight the importance of collaboration and coordination between healthcare levels, as well as of the continuity of care, to prevent prolonged hospital stays, early readmissions, and delays in identifying decompensations [18,19,20].

Managing CPCPs requires a comprehensive, personalised, and holistic approach, with continuous monitoring to mitigate the impact of coexisting diseases. The key lies in a multidisciplinary approach that integrates medical treatment, patient education, and social and psychological support [21]. Internationally, several models have been developed for chronic disease care [22], prioritising the effective management of complex chronic cases [23,24,25]. In Spain, regional health services have implemented various strategies and plans for chronic disease care, following the guidelines of the Ministry of Health and scientific societies [26]. Many of these models have incorporated the figure of the nurse case manager (NCM), although its impact has not yet been systematically evaluated [27,28].

Within this role, two areas of practice can be distinguished: the community NCM (CNCM), responsible for managing highly complex patients, with planning and coordination functions mainly within the primary care (PC) setting [29,30], and the hospital NCM (HNCM), who ensures the continuity of care and oversees resource management across different healthcare levels [31].

Although studies on case management in this patient population remain limited, their findings are consistent with improved health-related quality of life, therapeutic adherence, functional capacity, and a more efficient use of healthcare resources, including fewer avoidable hospitalisations and urgency visits [32,33,34,35,36]. Several studies conducted in Spain have also obtained favourable results with this model [37,38]. Moreover, a positive impact on caregiver overload has been reported in some studies through health education, emotional support, and better coordination of care [39,40]. All these effects appear to be greater when implemented in PC [41].

Based on the above, population ageing and the increasing burden of chronic diseases represent a significant challenge that requires solutions in the coming years. The NCM role could play a crucial part in addressing this issue. However, the available studies are limited by short follow-up periods and methodological heterogeneity due to variability in the indicators used and the patient profiles included. Therefore, further research with greater methodological rigour and longer follow-up periods is required.

## 2. Materials and Methods

### 2.1. Objective

The aim of the present study is to pilot CNCMs in assisting CPCPs dependent for activities of daily living (ADLs) with cardiac and/or respiratory pathologies and/or diabetes mellitus from PC and assess their effect on functional capacity, cognitive performance, quality of life, readmissions, clinical parameters, satisfaction with home care, and the overload of the main caregiver.

### 2.2. Design and Setting

A comparative trial will be carried out in the health area of Salamanca (Spain), particularly in the Garrido Sur and Miguel Armijo health centres. Both are urban and have a population with similar characteristics, so they will serve as the intervention and control centre, respectively. The PC nurses at both centres will continue to perform the usual interventions for CPCPs included in the Portfolio of Services of the Castilla y León Health System (SACYL), and case management will be added through a CNCM at the intervention centre.

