### 2.4. Sample Size Calculation

The sample size was calculated taking into account the main study variables. Specifically, it was estimated to detect a difference equal to or greater than 15 points in the Barthel Index, accepting an alpha risk of 0.05 and a beta risk of 0.2 in a bilateral contrast. Furthermore, the common standard deviation was assumed to be 34.8, as shown in the study by García-Fernández et al. [40], and a loss to follow-up rate of 20% was assumed due to the characteristics of the study subjects and the duration of follow-up. Therefore, it will be necessary to include 212 CPCPs (106 in each group) to detect statistically significant differences.

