### 2.8. Statistical Analysis

The normality of the variables will be analysed using the Kolmogorov–Smirnov test. Continuous variables will be presented as mean ± standard deviation, or as median and interquartile range in the case of a non-normal distribution. Qualitative variables will be expressed as number and percentage. The association between qualitative variables will be analysed with the chi-square test or Fisher’s test, as appropriate. Comparisons between quantitative variables will be carried out using Student’s *t*-test or the non-parametric Mann–Whitney U test for independent measurements and paired Student’s *t*-test for related measurements. A repeated-measures analysis of variance (ANOVA) will be performed to assess the effect of the intervention between study centres. Covariates will be included in the model to control for potential confounders such as baseline functional status, comorbidities, or characteristics of the main caregiver. An alpha risk of 0.05 will be set as the limit of statistical significance for bilateral hypothesis testing. Data will be analysed with SPSS statistical software version 28.0.

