## 5. Conclusions

This study might help to determine whether interventions led by CNCMs in PC offer benefits compared to usual follow-up for patients with complex chronic conditions and functional dependence. The resulting evidence may support decisions on the organisation of community-based care, promoting models that enhance care continuity, self-care, and health system efficiency.

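### With one centre per arm, intervention and centre cannot be separated, so the stated 80% power and 5% alpha hold only if no centre-level difference in outcome remains after adjustment

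*Protocol article*

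**What the plan says.** Section 2.2 names two health centres and justifies the pairing in one sentence: "Both are urban and have a population with similar characteristics, so they will serve as the intervention and control centre, respectively". Usual care continues in both, and "case management will be added through a CNCM at the intervention centre". Every patient at one centre is thus in the intervention arm and every patient at the other is a control.

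Section 2.4 sizes the trial on one outcome: "it was estimated to detect a difference equal to or greater than 15 points in the Barthel Index". The test is two-sided at the 5% level with 80% power. On the spread of scores the section says that "the common standard deviation was assumed to be 34.8". After a 20% allowance for losses it concludes: "Therefore, it will be necessary to include 212 CPCPs (106 in each group) to detect statistically significant differences". It mentions no ICC, design effect or between-centre variance.

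Section 2.8 states: "A repeated-measures analysis of variance (ANOVA) will be performed to assess the effect of the intervention between study centres". The covariates it gives as examples describe the patient or the caregiver.

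Section 2.9 allows for confounders that were not considered, and Section 4 lists the lack of randomisation and the small sample as limitations. Neither says that arm and centre coincide. Section 5 says, behind a cautious opening verb, that the study may contribute to an effort to "determine whether interventions led by CNCMs in PC offer benefits compared to usual follow-up".

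**The concern.** A between-arm comparison here is also a between-centre comparison. Anything that differs between the two centres and affects the Barthel Index over 12 months, such as staffing, organisation or local services, enters the estimated effect in full. Patient and caregiver covariates can remove measured imbalance in case mix. They cannot remove a centre-level effect, because a centre term in the model would be identical to the arm term. Adjusting for baseline removes a stable difference in starting level but not a difference between centres in change over time.

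The power and significance level are given without this condition. If a residual centre difference exists, the patient-level standard error is too small, a false positive is more likely than 5%, and power for the 15-point target is not 80%. Similar populations, the only justification offered, do not imply similar centres.

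**Working it through.** **Inputs.** From Section 2.4: difference 15, common SD 34.8, two-sided alpha 0.05, power 80%, losses 20%, 106 per group. From Sections 2.2 and 2.8: one centre per arm, analysed at patient level. The ICC is not in the document; 0.005 to 0.02 is an assumed range.

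**1. Reproducing the plan's figure.** For independent patients, n per arm = 2 × (1.96 + 0.8416)² × 34.8² / 15² = 84.5. Dividing by 0.8 gives 105.6, so 106 per group and 212 in total. The arithmetic is right. With 85 analysed per arm the standard error is 34.8 × √(2/85) = 5.34, and power is Φ(15/5.34 − 1.96) = 80.2%. This formula sets the between-centre variance to zero.

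**2. Adding a centre effect as a random component.** Keep the total SD at 34.8 and m = 85 per centre.
- Design effect: DE = 1 + 84 × ICC
- True standard error: SE = 34.8 × √(2 × DE / 85)
- Type I error of the patient-level test: 2 × [1 − Φ(1.96 × 5.34 / SE)]
- Power of a correctly sized test, if the ICC were known: Φ(15/SE − 1.96)

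| Assumed ICC | Between-centre SD (34.8 × √ICC) | DE | SE | Type I error | Validly sized power |
|---|---|---|---|---|---|
| 0 | 0 | 1.00 | 5.34 | 5.0% | 80.2% |
| 0.005 | 2.5 | 1.42 | 6.36 | 10.0% | 65.5% |
| 0.01 | 3.5 | 1.84 | 7.24 | 14.8% | 54.4% |
| 0.02 | 4.9 | 2.68 | 8.74 | 23.1% | 40.4% |

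Using the within-centre SD in the naive standard error instead gives type I errors of 10.1%, 15.1% and 23.6%, which is the same picture.

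**3. The same point without an ICC.** Suppose the two centres differ by a fixed 5 points for reasons unrelated to the intervention. With SE 5.34 the shift is 5/5.34 = 0.94 standard errors. The chance of a significant result with no intervention effect is then 15.5%. Power for a true 15 points is Φ(10/5.34 − 1.96) = 46.5% if the centre difference opposes the effect and Φ(20/5.34 − 1.96) = 96.3% if it favours it. A 2-point difference gives a false-positive rate of 6.6%.

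**4. Why more patients do not cure it.** Between-centre variance within an arm has zero degrees of freedom when the arm holds one centre, so the trial cannot estimate it. Larger centres shrink only the patient-level part of the error. At ICC 0.02 the power of the correctly sized test tends to Φ(15 / (34.8 × √0.04) − 1.96) = 57.7% however many patients are recruited. At ICC 0.005 and 0.01 the corresponding limits (99.1% and 86.2%) are above 80%, but that test needs an ICC the trial cannot supply. The planned test gets worse: at ICC 0.01 with 170 per centre, DE = 1 + 169 × 0.01 = 2.69, 1.96 × √(0.99/2.69) = 1.19, and type I error is about 23%.

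Steps 2 to 4 use a comparison of means at one time point as a stand-in for the repeated-measures model. That is also the basis on which Section 2.4 reproduces.

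**The case against.** The strongest reply is that the article is candid about its design. It calls the work a pilot, declares it non-randomised, warns of confounders, and hedges its conclusion. The two centres lie in one health area, work to one service portfolio, and were chosen for their similarity, so they are not random draws. This stands as a reason for moderate severity. It does not answer the point: the general caveats never say that arm equals centre, and the sample-size statement is unqualified. Naming the small sample as a limitation also suggests a remedy that would not help.

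A second reply is that the ICC figures apply to the unadjusted SD, whereas Section 2.8 adjusts for baseline function. This too has force. With an assumed baseline-outcome correlation of 0.6, and the ICC applied to the adjusted outcome, every standard error shrinks by √(1 − 0.6²) = 0.8. Power becomes Φ(15/5.09 − 1.96) = 84% at ICC 0.005, Φ(15/5.79 − 1.96) = 74% at 0.01 and Φ(15/6.99 − 1.96) = 57% at 0.02, against 94% with no centre effect. The tabulated powers may therefore be pessimistic. Type I error depends on a ratio of standard errors, so at a given residual ICC it is unchanged.

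A reader might also infer three stronger things that the document does not support:
- That the centres must be identical in every respect. The condition is only that no outcome difference remains after adjustment.
- That the true error rate is known to exceed 5%. No ICC is given, so the figures are illustrations.
- That evaluators are tied to one centre. Section 2.6 describes independent evaluators from the area's primary care management and does not link them to a centre.

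**Conclusion.** The concern holds in this form: intervention and centre are fully confounded, and the 80% power and 5% alpha are conditional on no residual centre-level difference in outcome after adjustment. The trial can neither guarantee nor estimate that condition. The sample-size arithmetic itself is correct.

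Under assumed ICCs of 0.005 to 0.02 on the unadjusted SD, with 85 analysed per arm, type I error would be about 10% to 23% and validly sized power about 65% down to 40%. A significant result alone could not be attributed to the case manager rather than the centre. This should be fixed, but it does not invalidate a study that presents itself as a non-randomised pilot with hedged conclusions.

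**What to change.** 1. **Section 2.4:** state that the 80% power and 5% alpha are conditional on no residual centre effect, and give the power over an assumed ICC range such as 0.005 to 0.02.
2. **Section 2.8:** add a sensitivity analysis that reports how large a centre difference, unrelated to the intervention, would remove the estimated effect.
3. **Sections 2.9 and 5:** say plainly that arm and centre coincide, and limit the inference to a comparison of two centres.

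A before-and-after comparison from historical records is tempting but should not be required. Records of admissions and drugs would not cover the Barthel Index, on which the trial is sized. The frailty and dependency data needed to identify past eligible patients may not exist.

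The cost is some wording and a small added analysis, with no extra patients. The stated power will look less favourable. None of these changes removes the confounding; they make the claims match what the design can support.

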### 2.3. Participants

This study will include CPCPs who, after being hospitalised due to decompensation of their underlying pathologies, present home care needs at discharge. To be identified as CPCPs, they must meet the criteria established by the Spanish National Health System, which include the presence of two or more clinical categories of pluripathology and at least one complexity criterion. The detailed list of criteria is provided in Table S1.

#### 2.3.1. Inclusion Criteria

The inclusion criteria are CPCPs with associated cardiac and/or respiratory pathologies and/or diabetes mellitus who present frailty criteria (Frail ≥ 1 point), require a main caregiver to perform ADLs (Barthel ≤ 60 points and/or grade II or III dependency recognised by Social Services), require home care and/or social resource management, and agree to sign (themselves or their legal guardians) informed consent to participate in this study.

#### 2.3.2. Exclusion Criteria

The exclusion criteria are patients with other pathologies associated with complex pluripathology, those with non-habitual caregivers, and those who reside outside the area corresponding to the Garrido Sur and Miguel Armijo health centres, despite being assigned to them.

### 2.4. Sample Size Calculation

The sample size was calculated taking into account the main study variables. Specifically, it was estimated to detect a difference equal to or greater than 15 points in the Barthel Index, accepting an alpha risk of 0.05 and a beta risk of 0.2 in a bilateral contrast. Furthermore, the common standard deviation was assumed to be 34.8, as shown in the study by García-Fernández et al. [40], and a loss to follow-up rate of 20% was assumed due to the characteristics of the study subjects and the duration of follow-up. Therefore, it will be necessary to include 212 CPCPs (106 in each group) to detect statistically significant differences.

### 2.5. Variables and Measurement Instruments

Most of the variables will be collected by means of hetero-administered questionnaires, except for those on caregiver overload and user satisfaction, which will be self-administered.

#### 2.5.1. Sociodemographic Variables

Data on age, sex, marital status, type of main caregiver (spouse, children, unpaid caregiver, or paid caregiver), and degree of dependency (II or III) will be collected at the initial assessment.

#### 2.5.2. Primary Outcome Measures

##### Activities of Daily Living (ADLs)

These will be assessed using the Barthel Index, validated in the Spanish population and showing good internal consistency (Cronbach’s alpha = 0.86–0.92), which evaluates a person’s ability to perform ten activities of daily living (eating, dressing and undressing, grooming, using the bathroom, sphincter control, bathing, moving around, and going up and down stairs), assigning up to 15 points to each according to the degree of autonomy. The minimum score is 0 and the maximum is 100. A person is considered totally dependent if their score is ˂20 points; severely dependent if it is between 25 and 60 points; moderately dependent if it is between 65 and 90 points; and mildly dependent if it is equal to 95 points [42].

##### Quality of Life

This will be assessed using the Spanish version of the COOP-WONCA test, which shows acceptable internal consistency (Cronbach’s alpha = 0.73). This instrument relates the patient’s quality of life to their health during the last four weeks by asking about their physical fitness, feelings, daily activities, social activities, state of health, changes in their state of health, and pain by means of a drawing representing a degree of functioning with a 5-level Likert scale. Higher scores express worse levels of functioning/well-being [43].

##### Cognitive Performance

This will be explored through the Montreal Cognitive Assessment (MoCA), which consists of 30 items and lasts approximately 10–12 min. It helps to identify mild impairments in cognitive skills (orientation, short-term memory/delayed recall, executive function/visuospatial ability, language, abstraction, identification, and attention). The total score is 30 points; a score of 26 or higher is considered normal. Cronbach’s alpha for the Spanish version was 0.77 [44].

#### 2.5.3. Secondary Outcome Measures

##### Clinical Variables

To assess some of the clinical variables, the devices listed below will be used and calibrated regularly according to the manufacturer’s recommendations:Blood pressure: the measurement will be taken using an OMRON M6 Comfort HEM-7321-E digital blood pressure monitor, taking three readings on the dominant arm with an interval of 1 min between them and using the average of the last two values according to the protocol of the European Society of Hypertension (ESH) [45].Heart rate and oxygen saturation: it will be determined using an approved Beurer PO 45 portable pulse oximeter.Capillary glycosylated haemoglobin: the test will be performed with a validated Abbott Afinion analyser after obtaining a capillary blood sample by finger prick, using a sampling device that is inserted into the test cartridge [46].Capillary blood glucose: a capillary fingerstick blood sample will be taken at least 2 h after the last meal. The test will be performed with an approved Freestyle Glucometer.Degree of dyspnoea: this will be examined using the modified Medical Research Council Scale (mMRC), which consists of 5 levels. The higher the level, the lower the tolerance to activity due to dyspnoea [47].Symptoms attributable to heart disease: these will be assessed using the New York Heart Association (NYHA) Functional Classification. Class I patients have no symptoms, while those in classes II, III and IV have mild, moderate, and severe symptoms, respectively [48].

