### 2.6. Data Collection

Data collection will be carried out by independent evaluators, who will be health professionals from the Salamanca Primary Care Management, with training in the use of the data collection form and the administration of the different tests, which will be paper-based.

The baseline assessment will take place at the patient’s home, and subsequent follow-up assessments will be arranged there or at the health centre depending on their progress:Initial assessment: the variables shown in Table 1 will be collected.Three-, six-, and twelve-month assessment: the same variables as in the initial assessment will be collected, adding the number of readmissions and medicines prescribed, as well as the evaluation of the satisfaction of the user and/or main caregiver.

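### Capillary glucose has only a lower limit on time since the last meal, so fasting and post-meal readings are pooled in one secondary outcome; recording hours since the last meal would remove avoidable variance and guard against timing shifts

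*Protocol article*

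**What the plan says.** Section 2.5.3 of the protocol article, under Clinical Variables, defines the glucose measurement: "a capillary fingerstick blood sample will be taken at least 2 h after the last meal". It states no upper limit, fasting requirement or time of day. The same paragraph is more exact about blood pressure, "taking three readings on the dominant arm with an interval of 1 min between them", with the last two values averaged. It also includes a second glycaemic measure: "Capillary glycosylated haemoglobin: the test will be performed with a validated Abbott Afinion analyser".

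Table 1 schedules the clinical variables at the initial assessment and at 3, 6 and 12 months. Section 2.6 places the first assessment at home, while "subsequent follow-up assessments will be arranged there or at the health centre depending on their progress". Section 2.2 gives each arm one health centre: "so they will serve as the intervention and control centre, respectively". Section 2.8 plans the comparison: "A repeated-measures analysis of variance (ANOVA) will be performed to assess the effect of the intervention between study centres". The covariates it gives as examples are "potential confounders such as baseline functional status, comorbidities, or characteristics of the main caregiver". Neither the variables described in Section 2.5 nor the rows of Table 1 include time since the last meal.

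**The concern.** A glucose reading two hours after a meal and one after an overnight fast measure different things. A rule with only a lower limit accepts both under one variable name. Two consequences follow, of unequal strength.

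- **Variance.** The spread between the two states is added to the spread between patients, which makes the glucose comparison less precise.
- **Possible bias.** If the mix of fasting and post-meal readings differs between centres, part of a glucose difference reflects when patients were seen. With one centre per arm, a local appointment pattern coincides with the arm.

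Clinical parameters are part of the study objective (Section 2.1) and are expected to improve (Section 3), so glucose is likely to be reported as evidence of effect. This is a rule that the article itself fixes, in a paragraph that sets out measurement conditions. It is not a detail left to a fuller document.

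**Working it through.** **1. The plan's own figure.** The only calculated figure is the sample size in Section 2.4, which is for the Barthel Index. Per group, 2 × (34.8 × (1.9600 + 0.8416) / 15)² = 84.49. Allowing for 20% loss, 84.49 / 0.80 = 105.6, so 106 per group and 212 in total. It reproduces, and nothing below changes it. The article gives no glucose SD, no gap between post-meal and fasting values, and no visit times.

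**2. Reading the rule.** A 2-hour post-meal sample satisfies the minimum, and so does a sample after an overnight fast. Pooling is therefore a direct consequence of the wording.

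**3. Variance.** Assumptions: gap between post-meal and fasting means of 30, 50 or 70 mg/dL; half of the readings fasting; SD within each state 50 mg/dL.

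Variance ratio = (SD² + p(1 − p) × gap²) / SD², with p = 0.5.

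| Gap (mg/dL) | Calculation | Variance ratio | SD ratio |
|---|---|---|---|
| 30 | (2500 + 0.25 × 900) / 2500 | 1.09 | 1.04 |
| 50 | (2500 + 0.25 × 2500) / 2500 | 1.25 | 1.12 |
| 70 | (2500 + 0.25 × 4900) / 2500 | 1.49 | 1.22 |

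An even split is the least favourable, since p(1 − p) is largest at 0.5. These ratios describe readings at one visit. In a within-patient change, the mixture adds nothing for a patient who is in the same state at both visits, and does add variance for patients whose state varies.

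**4. Centre comparison at a single visit.** Apparent difference = gap × difference between centres in the share of fasting readings. With an assumed 20-point difference in share: 30 × 0.20 = 6, 50 × 0.20 = 10 and 70 × 0.20 = 14 mg/dL, the centre with more fasting visits reading lower. With equal shares the difference is 0.

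**5. Comparison over time.** Glucose is also measured at the initial assessment. Write p for the share of fasting readings. The apparent effect on change from baseline is then, in size, gap × [(p at follow-up − p at baseline, intervention centre) − (p at follow-up − p at baseline, control centre)].

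- Stable habit in each centre: both brackets are 0, so the bias is 0 even if the centres differ throughout.
- The same shift in both centres: the brackets cancel.
- Shifts that differ by 20 points: 6 to 14 mg/dL again, by the arithmetic of step 4.

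A route to the third case exists on paper. Follow-up may move from home to the health centre according to the patient's progress, and progress is what the intervention aims to change. Visit hours could move with the setting. The article does not say that they do.

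**The case against.** The strongest reply is that baseline takes care of most of this. The clinical variables are collected at the initial assessment and the analysis is repeated-measures, so a lasting difference in appointment hours would largely drop out of the centre-by-time contrast. That stands. One limit is that Section 2.8 does not say which ANOVA term carries the intervention effect; a comparison of centres averaged over visits would not have this protection unless baseline glucose were adjusted for.

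Second, nothing shows that visit hours differ by centre. Section 2.6 describes trained, independent evaluators drawn from the area's primary care management rather than each centre's own staff, and one rule applies in both centres. This stands too, although the text does not secure equal timing.

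Third, a reader might infer that fasting and post-meal values could never be told apart later. The article does not support this. The paper form is not shown, an evaluator applying the 2-hour minimum has to ask about the last meal, and the covariates in Section 2.8 are given only as examples. What can be said is that the interval is not among the listed variables.

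Fourth, the sizes rest wholly on assumptions. Eligibility in Section 2.3.1 is cardiac and/or respiratory disease and/or diabetes, so not every participant need have diabetes, and one gap applied to everyone may be too large.

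The pooling itself and the variance it adds remain.

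**Conclusion.** The sampling rule pools two physiological states in one secondary outcome, and the listed variables give no means of separating them. The supported consequence is avoidable variance: 9% to 49% at a single visit, or 4% to 22% in SD, under an assumed gap of 30 to 70 mg/dL, an even mixture and a within-state SD of 50 mg/dL.

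A reader might go further and infer that a glucose difference between the centres would be an artefact of visit times, worth 6 to 14 mg/dL. The article does not support that. The figure needs either a 20-point difference in fasting share at a single visit or a 20-point difference in how that share changes after baseline, and neither is documented. It marks a risk that the plan leaves open and is not an estimate of bias.

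Severity is low. Glucose is one of several secondary clinical variables, does not enter the sample size, and is accompanied at the same visits by HbA1c, which does not depend on the timing of the last meal. The primary outcomes are unaffected.

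**What to change.** Record hours since the last meal at every assessment, and include it in the glucose analysis as a covariate whose value can change from visit to visit. Because glucose need not fall in a straight line with time, the interval can be entered in categories; alternatively, analyse fasting and post-meal readings separately. State that conclusions about glycaemic control rest mainly on the HbA1c already collected. Glucose can stay as a planned variable.

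The cost is one field on the paper form and one covariate. A conventional repeated-measures ANOVA takes covariates that are fixed per patient, so the glucose model should be one that accepts visit-level values, such as a linear mixed model. The field should be in place from the initial assessment, since the interval cannot be reliably recovered afterwards. The sample size of 212 does not change.
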